## Abstract

**Background:**

Sleep disturbance is common among those with cognitive impairment, potentially contributing to negative outcomes. Furthermore, growing evidence suggests that sleep disturbance is associated with the onset and progression of cognitive decline. There is therefore increasing interest in treating sleep disturbance in people with cognitive impairment.

Non-pharmacological treatments for sleep disturbance are unhindered by many of the adverse effects associated with pharmacological treatments, yet evidence supporting their use in clinical practice is often lacking. Cognitive behavioural therapy for insomnia (CBT-I) is the first-line treatment for insomnia and has demonstrated effectiveness in people with cognitive impairment in a small number of trials. Digital CBT-I (dCBT-I) overcomes many of the obstacles associated with accessing CBT-I (such as limited availability of therapists and transportation) whilst presenting others (such as internet access and digital literacy).

**Aim:**

To undertake a mixed-methods analysis of the usability and acceptability of a dCBT-I intervention (
*Sleepio*) among people with cognitive impairment.

**Methods:**

Participants will be community-dwelling adults aged ≥50 years with cognitive decline and probable insomnia. Study partners (being caregivers, family or friends of participants) will be recruited, if available, to examine how their involvement influences usability and acceptability.

Participants will be given access to
*Sleepio*, a fully automated and personalised dCBT-I programme delivered over the course of six weekly sessions. Usability and acceptability will be assessed by a bespoke questionnaire incorporating the System Usability Scale and the Usability Metric for User Experience - Lite (UMUX-Lite). Semi-structured interviews will explore participants’ experience of using the intervention.

**Conclusion:**

By examining barriers and facilitators to the usability and acceptability of
*Sleepio* among people with cognitive impairment, this study will provide insight into the potential efficacy of the intervention in this population whilst informing the design of a future definitive clinical trial.

## Introduction

Sleep is essential to maintain good physical and mental health
^
1–
3
^ and plays a central role in many physiological functions
^
4
^. Nevertheless, insomnia is common with approximately one-third of all adults experiencing insomnia symptoms
^
5
^, increasing to 75% in those aged over 65 years
^
6
^. Sleep patterns change as we age
^
7
^. Normal ageing is associated with reductions in total sleep time, sleep efficiency and slow wave sleep
^
8
^. Sleep disturbance is even more common among older adults with cognitive impairment
^
9
^. Compared to healthy aged-matched controls, people with mild cognitive impairment (MCI) experience reduced total sleep time, sleep efficiency and duration of REM, whilst sleep onset latency, wakefulness after sleep onset, and duration of stage one sleep are increased
^
10,
11
^.

Indeed, there is a well-established association between sleep disturbance and cognitive impairment
^
12
^, with evidence suggesting that the relationship may be causal and bi-directional
^
13
^. A meta-analysis of observational studies estimated that 15% of Alzheimer’s Disease may be attributable to sleep disturbance
^
14
^. Despite the recent Dementia Prevention, Intervention and Care: 2024 report of the Lancet Commission concluding that further research is needed to clarify the effect of sleep disturbance on cognitive decline
^
15
^, therefore, interest is growing in sleep disturbance as a potential modifiable risk factor for cognitive impairment
^
16
^. The European Academy of Neurology Brain Health Strategy, for example, has included sleep as a determinant of brain health
^
17
^.

Furthermore, sleep disturbance tends to worsen as cognitive impairment advances
^
18,
19
^, leading to deteriorating cognitive outcomes
^
20
^ and quality of life
^
21
^, as well as strained relationships with caregivers who experience considerable physical and emotional distress and burnout as a consequence
^
22,
23
^. The increased caregiver burden caused by sleep disturbance in people with dementia has been shown to lead to sub-optimal care
^
24
^ and early institutionalisation
^
25,
26
^. Sleep is therefore an important treatment target throughout the natural history of dementia, to potentially slow the progression of early-stage disease and to reduce the burden of symptoms in more advanced cases.

Pharmacological treatments for sleep disturbance are associated with a range of adverse effects, including sedation and increased risk of falls, headaches and dizziness
^
27
^. This has led to the American Geriatric Society Beers Criteria recommending against the use of pharmacological agents to treat sleep in older people
^
28
^. Additionally, there is evidence to suggest that pharmacological treatments to improve sleep can worsen cognitive function in older people
^
13
^. There is therefore increasing focus on exploring non-pharmacological approaches to treating sleep disturbance among older people with cognitive impairment
^
29
^.

Cognitive behavioural therapy for insomnia (CBT-I) is the first-line treatment recommended for insomnia and is supported by a large evidence base
^
30–
33
^. A recent meta-analysis of controlled clinical trials of sleep treatments for people with cognitive impairment included two trials of CBT-I and both demonstrated significant improvements in sleep
^
34
^. One of the trials, involving 28 participants from independent living facilities, achieved significant improvement in both subjective and objective measures of sleep using the Insomnia Severity Index (ISI) and wrist actigraphy respectively
^
35
^. The other trial, involving 35 participants recruited from outpatient clinics, found no improvement in objective sleep measures, with significant improvements only in subjective sleep quality
^
36
^. Participants in the latter trial did not have significant sleep disturbance at baseline, however, and it is perhaps for this reason that meta-analysis of the two trials did not find any significant effect on sleep. Given the promising results in the trial that included participants with sleep disturbances at baseline, there is a need to further investigate the potential application of CBT-I to treat sleep disturbances among people with cognitive impairment.

Unfortunately, however, CBT-I is often difficult to access for many due to the shortage of trained therapists
^
37
^. Digital CBT-I (dCBT-I) provides a possible solution to overcome the barriers associated with accessing the traditional therapist-delivered model of CBT-I. Indeed, evidence demonstrates the effectiveness of dCBT-I
^
38,
39
^, which has also recently been shown to be feasible and effective in older people
^
40
^. A small mixed-methods study involving 12 participants has demonstrated preliminary acceptability of dCBT-I (SHUTi OASIS) among older people with MCI
^
41
^. More recently, a small open-label randomised controlled feasibility trial demonstrated preliminary efficacy of dCBT-I (
*Sleepio*) in improving the ISI of people with MCI
^
42
^. This latter trial was conducted remotely, indicating that the participants likely had relatively mild deficits and were adept at using digital technology. A recent qualitative study, conducted among patients who were recovering from stroke, identified some difficulties accessing and operating the
*Sleepio* programme
^
43
^. Nevertheless, nine out of a total of eleven participants successfully completed the programme, although three did require the assistance of their respective caregivers to do so.

It has been suggested that more qualitative research is required to explore barriers and facilitators to the uptake and acceptability of alternative modes of delivery of CBT-I, such as dCBT-I
^
44
^. By its exploratory and inductive nature
^
45
^, qualitative research can provide more nuanced and subtle insights into the participants’ perspective of how interventions are delivered in practice
^
46
^, thus helping to guide the design of future interventions and clinical trials.

## Aim

Given the importance of treating co-morbid sleep disturbance at all stages of cognitive decline, we propose to undertake a mixed-methods analysis of the usability and acceptability of dCBT-I (
*Sleepio*) among people with varying degrees of cognitive decline, ranging from subjective cognitive decline (SCD) through to MCI and mild-moderate dementia. We will also endeavour to assess whether usability and acceptability can be improved by the availability of a study partner to assist with operation of the dCBT-I (
*Sleepio*) programme. This will help to determine which people with cognitive impairment may be able to use and benefit from dCBT-I (
*Sleepio*) to treat co-morbid sleep disturbance.

## Methods

### Intervention

*Sleepio* is a fully-automated and personalised dCBT-I intervention designed to treat insomnia using a combination of cognitive, behavioural, sleep hygiene and relaxation techniques. It is delivered through a web-based platform, supporting iOS or Android mobile applications. Underlying algorithms organise the delivery of information, support, and advice in a manner tailored to each individual patient based on their responses to an initial sleep study questionnaire and subsequent daily sleep diary entries throughout the duration of the programme. The programme consists of six sessions, each between five and twenty minutes in duration.
*Sleepio* can be completed within a six-week period. However, the average time taken to complete the programme is 9–10 weeks. No time restriction is placed on the user to complete the sessions, and all previously viewed sessions remain available to the user to re-watch throughout the duration of the programme. Participants are offered daily notifications to prompt adherence to the programme.

### Participants

Potential participants will be community-dwelling adults aged fifty years and older with probable insomnia attending outpatient memory clinics affiliated with the Mercy University Hospital in Cork, Ireland. Only participants with probable insomnia will be included because, although previous studies have suggested the effectiveness of
*Sleepio* in sub-clinical insomnia
^
47
^, other studies have demonstrated that participants’ motivation to adhere to the
*Sleepio* programme was proportional to the severity of their sleep disturbance
^
43
^. Study partners, if available, will also be recruited for dyadic participation and may include caregivers, family members or friends attending memory clinic with the participants. A previous qualitative study of the usability of
*Sleepio* amongst patients following stroke found that some had to rely on help from partners to operate the programme and suggested that more people may be able to use dCBT-I if given support from a partner or caregiver
^
43
^. It is anticipated that study partners may play an important role in facilitating successful adherence of participants to the
*Sleepio* programme, particularly among participants with more advanced cognitive impairment
^
48
^. While ideal and likely to enrich the study, the availability of a study partner will not be an inclusion/exclusion criterion. We will nevertheless endeavour to include them when available. Other inclusion/exclusion criteria are as follows:

Inclusion criteria:

1. Aged ≥50 years.2. Sleep Condition Indicator (SCI)
^
49
^ Score ≤16/32. The SCI is an 8 item scale validated to assess insomnia based on DSM-5 criteria. Scores range from 0–32, with scores ≤16 indicating probable insomnia.3. Established SCD, MCI or mild-moderate dementia, diagnosed by a consultant physician specialised in cognitive disorders prior to enrolment in the study. Dementia will be defined using DSM-5 classification and staged according to the Reisberg FAST scale
^
50
^ into early/mild/moderate stage. MCI will be defined using Petersen’s criteria
^
51
^. Participants must score between 0 – 2 on the Clinical Dementia Rating (CDR) scale
^
52
^, a commonly used clinician-rating scale of global symptom severity in dementia.4. Sufficient physical/sensory (visual/hearing) capacity to use the intervention, as judged by the clinician/investigator.5. English-speaker (intervention only available in English).6. Community-dwellers (non-institutionalised).7. Ability to provide informed written consent.

Exclusion criteria:

1. Known history of an International Classification of Diseases (ICD) defined sleep disorder other than insomnia disorder.2. Receipt of a sleep-related cognitive behavioural therapy intervention within the past six months.3. CDR >24. Severe depression (defined as depression requiring hospitalization in the past 12-months or visit to psychiatry outpatient clinic in the past three months).5. Unstable depression/anxiety disorders or panic attacks (unstable will be defined as changes in antidepressant medications within the last three months - i.e. no start, stop or change in dose).6. Other relevant major neuropsychiatric disorders, including schizophrenia, psychosis, mania, bipolar affective disorder, epilepsy or seizure disorder.7. Ongoing substance or alcohol abuse.8. Long-term physical or sensory impairment, pain or other medical condition which, in the opinion of the principal investigator, could impair participation for reasons other than cognitive impairment.9. Planned surgery or hospitalisation during the study that could interfere with participation.10. Medical conditions rendering the patient too unwell to continue to participate in the study in the opinion of the principal investigator.11. A change in the following medication within the three months prior to enrolment:a. Benzodiazepine and non-benzodiazepine hypnotic or anxiolytics agentsb. Cholinesterase inhibitors or Memantinec. Antidepressantsd. Antipsychoticse. Amphetamine derivativesf. Decongestantsg. Narcotic analgesicsh. β-Blockersi. Pulmonary medications (Theophylline and Albuterol)j. Melatonin

### Recruitment

All patients attending memory clinics affiliated with the Mercy University Hospital in Cork, Ireland will be screened for eligibility. Consecutive patients who meet eligibility criteria will be invited to participate in the study. It is hoped to recruit 20–30 participants over a four month period. Where possible, study partners including friends or family members of participants, will be recruited to support participants throughout the study.

### Consent process

Fully informed written consent will be obtained from each participant prior to enrolment. The capacity of all participants to provide valid informed consent to participate in the study will be determined by a consultant physician in geriatric medicine. Fully informed written consent to participation will also be obtained from study partners (caregivers, friends, and or family members) if available and willing to participate. Participants and their study partners (if applicable) will be provided with a Participant Information Leaflet detailing the purpose of the study and what participation in the study would entail for them. Copies of the Participant Information Leaflet and Consent Forms that will be used in the study are available in the extended data.

### Enrolment

Once recruited, participants will be provided with access to the study intervention (
*Sleepio*). Given the digital nature of the intervention, each participant’s digital literacy will be assessed using the Mobile Device Proficiency Questionnaire
^
53
^. Every participant will be provided with a training/orientation session to teach them how to use the
*Sleepio* programme. Additionally, each participant will be provided with clear written instructions on how to access and use the
*Sleepio* programme. If a study partner is available, and both the participant and the study partner consent to their participation in the study, the partner will be also included in the training session.

### Data collection

Data collection will be carried out in accordance with the European Union’s General Data Protection Regulation and local data protection policies. The following data will be recorded in respect of every participant at baseline:

Demographic data, including: age, sex, marital status, level of education, and employment status.Charlson Co-morbidity Index
^
54
^
Cognitive diagnosis and stage of cognitive impairmentMedications

Following completion of the
*Sleepio* programme, usability and acceptability will be assessed initially by a bespoke questionnaire incorporating the System Usability Scale
^
55
^, adapted for cognitive impairment
^
56
^, and the Usability Metric for User Experience - Lite (UMUX -Lite)
^
57
^. The System Usability Scale is a validated and commonly employed 10 item Likert-type scale that provides a global assessment of how user-friendly a system or product is perceived to be. The UMUX-Lite is a more condensed two item Likert-type scale that also measures user-satisfaction with a system or product. Finally, participants and their study partners (where applicable) will be interviewed to further assess the usability and acceptability of the programme. The interview will be audio-recorded and conducted in a semi-structured manner using the topic guide included in the supplementary material. Participants and their study partners will be asked to expound on any difficulties they had in complying with the programme and whether they found the programme beneficial. In order to reduce the possibility of social desirability and positivity bias, the participants and their study partners (where applicable) will be informed that the interviewer is not affiliated with
*Sleepio* and that the objective of the study is to obtain an accurate understanding of their experience using the programme in order to guide future research.

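### Every usability and acceptability measure is triggered by completing a programme that has no time limit, and no route is given for assessing people who stop or stall

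*Protocol article*

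**What the plan says.** The Data collection section first lists baseline data to be recorded for every participant. It then turns to the outcome measures: "Following completion of the *Sleepio* programme, usability and acceptability will be assessed initially by a bespoke questionnaire". That questionnaire contains the SUS and the UMUX-Lite. The interview is placed last in the sequence, and no other usability or acceptability assessment is described.

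On duration, the Intervention section says "No time restriction is placed on the user to complete the sessions" and that "the average time taken to complete the programme is 9–10 weeks". The article does not define completion for study purposes, set a cut-off date for assessment, or describe an assessment at stopping.

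The Data analysis section reports mean SUS and UMUX-Lite scores. It names no denominator and no handling of people who do not finish.

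The Aim is to learn which people with cognitive impairment can use and benefit from the programme. The Discussion adds barriers and facilitators, and the influence of digital literacy and study partners.

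**The concern.** Not finishing is among the clearest signs that a programme is hard to use. Here it is also what keeps a person from being measured, so the outcome helps decide who contributes data. With no deadline and no study cut-off, someone who stalls has no defined moment at which an assessment falls due.

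The article itself expects such difficulties. The Discussion says that reduced ability to understand, learn and remember may limit this kind of therapy, perhaps more so in digital form. The Participants section expects study partners to matter most in more advanced impairment. Losses would therefore probably fall on people with more impairment, lower digital literacy or no partner. Any comparison by these factors would then be made only among those who managed to finish.

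For the interviews, the accounts lost are those of people whose barriers were not overcome. An analysis plan cannot repair this later, because the ratings and interviews would never have been collected.

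**Working it through.** The article has no sample-size or precision calculation, so there is no figure of its own to reproduce.

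**Inputs from the article**
- Planned size (Recruitment): "It is hoped to recruit 20–30 participants over a four month period". So N = 20 to 30.
- Completion of the same programme after stroke (Introduction): "nine out of a total of eleven participants successfully completed the programme, although three did require the assistance of their respective caregivers to do so". So c = 9/11 = 0.818, and 1 − c = 2/11 = 0.182.

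**Input assumed**
- d, the gap in mean SUS between completers and non-completers. The article gives none. The range used is 10, 20 and 30 points on a scale taken as 0 to 100.

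**Step 1: people not measured.** Expected number = N × (1 − c).
- N = 20: 20 × 2/11 = 3.6
- N = 30: 30 × 2/11 = 5.45

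This is about 4 to 5 people, leaving about 16 to 25 assessed.

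**Step 2: chance of losing at least one.** 1 − c^N.
- N = 20: 1 − (9/11)^20 = 0.982
- N = 30: 1 − (9/11)^30 = 0.998

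**Step 3: shift in the mean.** Let M_c and M_n be the means of completers and non-completers. The mean over both groups is c × M_c + (1 − c) × M_n. The completer-only mean exceeds it by (1 − c) × (M_c − M_n) = (1 − c) × d.
- d = 10: 0.182 × 10 = 1.8 points
- d = 20: 0.182 × 20 = 3.6 points
- d = 30: 0.182 × 30 = 5.5 points

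**Step 4: how firm is 9/11?** The exact 95% interval for 9/11 is 48% to 98%, so non-completion between about 2% and 52% is compatible with that one small study, and it was in a different population.

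**A pessimistic variant.** Three of the nine completers needed a caregiver's help. If nobody had help and all three would otherwise have failed, completion would be 6/11 and non-completion 5/11. That gives 9.1 (N = 20) to 13.6 (N = 30) people unmeasured, and shifts of 4.5, 9.1 and 13.6 points for the same three gaps. It is not the main case, because the study recruits partners where available.

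**The case against.** The strongest case on the other side is that the article nowhere says non-completers are excluded. The completion wording may be ordinary sequencing: baseline, programme, follow-up. The interview sentence is not restricted to completers and asks about difficulties in complying, which presupposes imperfect adherence. The topic guide and information leaflets are extended data that are not shown here, and the full protocol may cover people who stop. The study is also small and descriptive, with no SUS threshold or go/no-go rule.

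Part of this stands. Completer-only assessment is a consequence of the stated trigger, not a declared exclusion, and other study documents may be better worded. But the article does state the trigger. The compliance question comes after that trigger, and nothing says it is put to people who have stopped. If completion was meant as the end of participation, the text needs to say so and define that end.

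A reader might infer more than the article supports:
- **A contradiction over duration.** The abstract describes "a fully automated and personalised dCBT-I programme delivered over the course of six weekly sessions", while the Intervention section reports a longer average and no limit. These are compatible: the same section says six weeks is possible, so one describes the designed pace and the other the pace seen in practice.
- **Recall error from an unlimited wait.** Under the rule as written, those who are rated are rated after finishing. Those who stall are not rated at all, so the open-ended delay does not lie between use and rating.
- **Non-completion that can never be seen.** The programme uses daily diary entries, and the cited stroke study counted completers. What is missing is a study cut-off, not the means to observe stopping.
- **A large, known bias.** The score gap has no source in the article, so no particular number of points can be claimed.

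**Conclusion.** The concern holds as a flaw in the assessment trigger. All outcome measures hang on completing a programme without a deadline, and the article provides no assessment for people who stop or stall. Scores and themes would come from those able to finish, which works against the study's own aim.

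The upward direction of the bias requires only that people who stop would, on average, rate the programme lower. That is likely, but it is not shown in the article. The size is uncertain: about 4 to 5 of 20–30 participants unmeasured if the stroke study's completion rate carries over, and a 1.8 to 5.5 point overstatement of mean SUS under the further assumption of a 10 to 30 point gap. The loss of these people's accounts of barriers does not depend on any assumed SUS gap.

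**What to change.** In Data collection, replace the completion trigger with: 'at completion, at stopping, or at a pre-set assessment date after access is given, whichever is first, in every enrolled participant'. State the date in advance. It governs measurement only; access to the programme is unaffected.

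Then:
- Invite people who stop to the questionnaire and to an interview that includes reasons for stopping.
- Report completion and the number of sessions completed for all enrolled.
- Report SUS and UMUX-Lite means for everyone who used the programme at least once, with completers as a secondary set. A mean over all enrolled is not possible, because someone who never used the programme cannot meaningfully rate it.
- Count never-starters separately, with their reasons.

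The cost is a few extra contacts with people who have stopped, an ethics notification, and a mean score that will probably look less favourable. No additional participants are needed. The change has to be in place before outcome data are collected, since missed assessments cannot be recovered at analysis.
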